# Interim pressure garment therapy (4–6 mmHg) and its effect on donor site healing in burn patients: study protocol for a randomised controlled trial

**DOI:** 10.1186/s13063-016-1329-x

**Published:** 2016-04-26

**Keywords:** Interim compression garment, Donor site, Burns, Occupational therapy

## Abstract

**Background:**

Pressure garment therapy (PGT) is well accepted and commonly used by clinicians in the treatment of burns scars and grafts. The medium to high pressures (24–40 mmHg) in these garments can support scar minimisation, and evidence is well documented for this particular application. However, PGT specifically for burn donor sites, of which a sequela is also scarring, is not well documented. This study protocol investigates the impact of a low pressure (4–6 mmHg) interim garment on donor site healing and scarring. With a primary purpose of holding donor dressings in place, the application of the interim pressure garment (IPG) appears to have been twofold. IPGs for donor sites have involved inconsistent application with a focus on securing wound dressing rather than scar management. However, anecdotal and observational evidence suggests that IPGs also make a difference to some patient’s scar outcomes for donor sites. This study protocol outlines a randomised controlled trial designed to test the effectiveness of this treatment on reducing scarring to burn donor sites.

**Methods/design:**

This study is a single-centre, single (assessor)-blinded, randomised control trial in patients with burns donor sites to their thighs. Patients will be randomly allocated to a control group (with no compression to donor sites) or to an experimental group (with compression to donor sites) as the comparative treatment. Groups will be compared at baseline regarding the important prognostic indicators: donor site location, depth, size, age, and time since graft (5 days). The IPG treatment will be administered post-operatively (on day 5). Follow-up assessments and garment replacement will be undertaken fortnightly for a period of 2 months.

**Discussion:**

This study focuses on a unique area of burns scar management using a low-pressure tubular support garment for the reduction of donor site scars. Such therapy specifically for donor scar management is poorly represented in the literature. This study was designed to test a potentially cost-effective scar prevention for patients with donor sites to the thigh. No known studies of this nature have been carried out to date, and there is a need for rigorous clinical evidence for low-pressure support garments for donor site scar minimisation.

**Trial registration:**

Australian New Zealand Clinical Trials Registry identifier ACTRN12610000127000. Registered 8 Mar 2010.

## Background

Thickened erythematous scars can reduce physical function and create a distorted physical appearance for a burn-injured patient [1–3]. When a burn penetrates deeply enough into the dermis of the skin, surgery is often required to assist healing. The surgery involves removing the burned or dead skin (debriding) and replacing it with a thin section of unburned healthy skin (donor skin), known as a split-thickness skin graft (SSG). This donor skin is surgically removed, commonly from the patient’s own thigh area, using a dermatome at a measure of 8/1000 inch to 12/1000 inch (depending on the thickness required to heal the burn defect) and includes the epidermis and the upper third of the dermis [4, 5]. The tissue removed for a SSG is comparable in depth to a partial thickness skin loss [5]. The remaining exposed area of dermis is referred to as the *donor site*. The donor skin is then placed over the original debrided burn wound area to assist in healing. There are sufficient residual epidermal cells in the remaining dermis to allow re-epithelisation to occur over an approximately 14-day period [4]. The donor site wounds discussed in this paper are routinely dressed with ALGISITE, ACTICOAT, MELOLIN, and HYPAFIX (all from Smith & Nephew, Andover, MA, USA) and heavy crepe bandage immediately post-operatively until wound review day 3 or 5. After this time, the donor site is then dressed with soft white paraffin (Kenkay Pharmaceuticals, Smeaton Grange, NSW, Australia), Xeroform (DeRoyal, Powell, TN, USA), and HYPAFIX or heavy crepe bandage until the wound is considered healed (no raw, open or oozing epithelium). Interim pressure garments (IPGs) for donor sites are routinely provided to inpatients at the [name] Burns Centre, as early as day 1 post-operatively with a focus on securing wound dressings rather than scar management.

Despite the donor site depth being extremely thin, patients often describe this new wound to be like ‘bad gravel rash’ and report worse pain in this wound than at the original burn or graft site. Pain associated with burn surgery has been shown to delay patients’ return to work and daily functional activity, with donor sites consistently identified as a potential source of concern for burn patients [1–3, 6–8]. Protection and support of the remaining epidermal and dermal elements of this surgical wound (donor site) are required to assist effective tissue healing with minimal scarring [4, 5, 9–12].

A review of the literature published over the past decade demonstrates the advances made in minimising scar formation [13–15]. Compression garment therapy has been used since the early 1970s to aid healing of burns scars and graft sites [9, 11, 16–20]. It is believed that this is accomplished primarily by applying pressure to the healing burn wound with a medium- to high-pressure garment. The definition of medium to high pressure for burn garments has been reported in the literature to be between 20 mmHg and 40 mmHg [17, 21]. However, pressures as low as 15 mmHg have also been reported as being effective [15, 17, 22].

Pressure garments appear to enhance the scar maturation process following epithelisation and, if worn for a minimum of 20–23 h/day, also appear to inhibit the development of hypertrophic or abnormal scar tissue. Although the exact mechanism of scar reduction remains largely unknown [23], it is assumed to be due to the garment gently restricting blood flow to the scar surface area and reorganise collagen fibres to resemble that of normal skin through a constant external pressure to the skin surface [9, 10]. The reduction of capillary filtration into the wound bed has also been reported to assist in the reduction of pain for these patients [13, 24]. It is thought that the increased blood rush caused by gravity when standing, and particularly when the patient is mobilising, stretches the fragile surface of the donor site wound, resulting in pain [1–3, 6–8].

The pressure garment is positioned over any dressings that may be needed in the early stage of recovery and is worn until the burn scar has matured or become pale in colour, resembling normal skin. This process of scar maturation is reported to take 18–24 months to complete, but it can take longer in some cases [6, 8, 11, 19, 20]. Although it is an accepted intervention in reducing scar formation following a burn, the effectiveness of pressure garment therapy has not been scientifically assessed on donor site scars [6, 8, 9, 11, 16–21, 25, 26].

As an alternative, the gentler ‘interim’ garment (termed an *interim pressure garment* for the purpose of this study) can be applied post-operatively around days 3–5 before donning the firmer compression garment. These interim garments are made from a tubular elastic material (similar to Lycra® bicycle pants) (Fig. 1a) and apply a gentle supportive pressure over the thigh and donor site areas [7, 27].

### Primary objectives

This research study aims to establish evidence for tissue support (4–6 mmHg) in healing burn donor sites and to test the use of interim garments made from tubular support bandages for donor site scar management. Specific aims are to investigate whether low-pressure IPG support to donor sites compared with no IPG results inReduction of time to epithelisationReduction of erythemaReduction of scar thickness and/or heightImprovement of overall scar appearanceReduction of self-reported pain levels

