### Measurement tools

In this study, the commercially available, evidence-based measurement tools described below will be used. These outcome measures will be done every 2 weeks for a period of 2 months.

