### Sample size

Previous studies using the DermaScan C have shown an effect size of 2.35 (1.69–3.01) between skin-thickness measurements of donor sites and scar sites [22]. For a minimum clinical difference of 0.5 mm between groups of less than 0.05 and a power of 0.9, 22 subjects per group would be required [22, 40] (assuming a standard deviation of 0.5 mm for wound thickness).

On the basis of data obtained from January 2013 to May 2015 (where patients admitted to the RBWH [name] Adult Burns Centre are represented as males = 593 admissions and females = 237 admissions), the ratio is expected to be 3:1. This ratio should accurately reflect the distribution of burns within the general community.

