### Proposed data analysis

Groups will be compared at baseline regarding the important prognostic indications: donor site location, depth, size, age, skin type and time since graft. Data will be entered into IBM SPSS 22.0 for Windows software files (IBM, Armonk, NY, USA) and tested for normality of distribution. Descriptive statistics for all variables will be computed. If parametric statistics are able to be used, a two-way analysis of variance for group × time interaction will be performed to compare skin thickness between normal, donor and scar sites with a planned least significant difference post hoc analysis. Significance will be set at *p* < 0.05. If raw data are not normally distributed, an equivalent non-parametric analysis will be used [40].

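### Five outcomes share primary status under one p < 0.05 threshold, with no single primary outcome or time point, while the sample size covers thickness only

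*Protocol article*

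**What the plan says.** Under Primary objectives, the article says: "Specific aims are to investigate whether low-pressure IPG support to donor sites compared with no IPG" leads to five improvements: faster epithelisation, less erythema, less scar thickness and/or height, better overall scar appearance, and less self-reported pain. They form one flat list, and none is called the primary outcome.

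Under Measurement tools: "These outcome measures will be done every 2 weeks for a period of 2 months". No visit is singled out as decisive.

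Under Sample size, the calculation concerns thickness alone: "For a minimum clinical difference of 0.5 mm between groups of less than 0.05 and a power of 0.9". Its spread is given as follows: "assuming a standard deviation of 0.5 mm for wound thickness". The result is 22 per group. The section does not call thickness the primary outcome.

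Under Proposed data analysis, the main model is this: "a two-way analysis of variance for group × time interaction will be performed to compare skin thickness between normal, donor and scar sites". The same sentence attaches pairwise follow-up tests that carry no multiplicity correction: "with a planned least significant difference post hoc analysis". The threshold is given once: "Significance will be set at *p* < 0.05". The section names no analysis for the other four aims beyond descriptive statistics, and no adjustment or testing order.

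**The concern.** The Discussion foresees two conclusions: the garment is shown to help donor-site healing, or it makes no difference, with consequences for budgets. Five outcomes have equal standing and the text does not say which one decides. A significant result on any of them could therefore be presented as meeting a primary objective, and the 5% threshold would not be the error rate of that claim.

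The stated power has the mirror-image problem. The 90% describes thickness and says nothing about the other four aims. Self-reported pain, and the patient's part of the scar scale, come from participants who know whether they wear a garment. As the text stands, such a result carries the same weight as the instrument measurement for which the trial was sized.

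**Working it through.** **1. The plan's own figure.** Inputs from Sample size: difference 0.5 mm, SD 0.5 mm, power 0.9. The wording around 0.05 is garbled; I read it as alpha.
- n per group = 2 × (1.960 + 1.282)² × (0.5/0.5)² = 21.01, rounded up to 22.
- A one-sided test would give 17.13, so 18. The stated 22 therefore implies a two-sided 5% test.
- By t-test, the requirement is 22.02 and power at 22 per group is 0.900.

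The 22 reproduces for thickness, tested once at two-sided 5%.

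**2. One test per outcome.** Inputs: five aims (Primary objectives) and threshold 0.05 (Proposed data analysis). The correlation between outcomes is not in the article, so it is an assumption, shown over a range.
- Independent outcomes: 1 − 0.95⁵ = 1 − 0.7738 = 0.226.
- For equally correlated two-sided normal tests, the chance of at least one false positive is:

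| Assumed correlation between outcomes | Chance |
|---|---|
| 0 | 22.6% |
| 0.3 | 20.9% |
| 0.5 | 18.3% |
| 0.7 | 14.8% |
| 0.8 | 12.7% |
| 0.9 | 10.2% |

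**3. If each visit were also tested without adjustment.** The article does not state this, so the result is conditional. Fortnightly review over 8 weeks gives four visits. Time to epithelisation is one value per patient and is counted once, so there are 1 + 4 × 4 = 17 tests.
- One outcome at four visits: 15.6% at an assumed visit correlation of 0.5, and 9.4% at 0.9.
- All five aims, outcomes independent, visit correlation 0.5: 1 − 0.95 × (1 − 0.156)⁴ = about 52%.
- All five aims, outcome correlation 0.7, visit correlation 0.9 (simulation): about 24%.

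The range is thus about 24% to 52% for outcome correlations of 0 to 0.7 and visit correlations of 0.5 to 0.9. If the post hoc tests were run only after a significant overall test, inflation would be smaller; I did not model that.

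**4. Splitting alpha instead of ranking.** Five equal shares give 0.05/5 = 0.01 each.
- Power for 0.5 mm at 22 per group falls from 90% to 73% by t-test (77% by normal approximation).
- Restoring 90% needs 31.5, so 32 per group by t-test (30 by normal approximation), against the planned 22.

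**The case against.** The best defence is that the article only summarises a fuller protocol. A testing order or multiplicity rule is commonly kept there or in the analysis plan, so the lack of a correction is not in itself a defect. That is fair. It does not remove what the article does state: five aims with equal primary status, one threshold, and a sample size for only one of them.

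A reader might infer that all five outcomes are tested at every visit with least-significant-difference tests. The text does not support this. The two-way analysis and its post hoc step are tied to skin thickness, and time to epithelisation cannot be tested by visit. The visit-wise range in the working therefore shows what could happen, not what is planned. Counting five outcomes at four visits as 20 tests would also overstate it.

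A reader might also take 15% to 23% as the trial's established error rate. That is too strong. The range counts one test per outcome, assumes correlations of 0 to about 0.7 that the article does not give, and requires that any single success counts as a primary claim. The article states no success rule in either direction.

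Finally, blinding of the assessor only is openly declared and is not a multiplicity error. It matters here only because self-reported outcomes stand level with the measured one.

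**Conclusion.** The concern holds in limited form. Five unranked primary aims share one 5% threshold, no deciding outcome or time point is named, and only thickness is sized. With one test each, and if any one success supports a primary claim, the chance of at least one false positive is 22.6% under independence, about 15% at correlation 0.7 and about 10% at 0.9. Even at the strongest correlation considered it is twice the nominal 5%. Separate visit-wise testing would raise it further, but the article does not commit to that. The direction is secure; the exact size rests on assumed correlations. The weakness should be corrected, and it does not invalidate the design: the sample size is sound for the one outcome it addresses.

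**What to change.** - Name donor-site thickness by DermaScan at one stated time point as the single primary outcome. The end of the 8-week treatment period is a natural choice. Thickness is the only outcome the sample size supports.
- Make time to epithelisation, erythema, overall appearance and pain secondary, tested in a fixed order or with Holm correction. Label patient-reported pain and scar scores as unblinded.
- For thickness, report group differences at each visit with confidence intervals rather than relying on unadjusted least-significant-difference tests.

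Ranking is preferable to splitting alpha, which would cut power for thickness to about 73% or require about 32 per group.

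Cost: four outcomes lose primary status. No extra participants or measurements are needed. The trial is registered, has two ethics approvals and reports eight pilot participants recruited, so a registry update or ethics amendment may be needed. The choice should be fixed before outcome data are compared by group.

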## Methods/design

### Protocol and registration

The methodology has been documented in a protocol and registered on a publicly available site (Australian New Zealand Clinical Trials Registry [ACTRN] identifier 12610000127000). The methods are summarised here according to the revised Consolidated Standards for Reporting Trials (CONSORT) statement [28].

### Design

The clinical trial has been designed as a single-centre, prospective, single-blind randomised controlled trial.

### Randomisation

Randomisation will be achieved through computerised tabulation with concealed allocation to each participant via a sealed envelope method. Participants will be randomly allocated into one of two groups: a control group that will have no compression to donor sites (the standard existing treatment) or an experimental group that will be provided with compression to donor sites (the comparative treatment).

### Eligibility

All new patients admitted to the [name] Adult Burns Centre who require SSG surgery for burn management over less than 15 % of their total body surface area (TBSA) will be screened for eligibility to participate in the study by the principal investigator.

**Table Taba:** 

*Inclusion criteria*	*Exclusion criteria*
Donor site located on one thigh only (measured to be 10 cm above the patella)	Burns to left, right or both thighs
Male or female	Donor site at anatomic location other than the thigh,
Older than 14 years of age (with adult consent) and able to provide informed consent	A psychiatric history documented in the medical chart which could cause a variable outcome (high risk of non-compliance)
	A pre-existing co-morbidity associated with delayed healing
	Arterial disease and/or vascular compromise as previously documented in the medical chart
	A dermatological condition in the region where the donor site needs to be taken
	Allergy to ultrasound gel
	Medications that may impact on wound healing
	Consent not given

If eligibility is established, patients will be approached by the principal investigator and a lay explanation of the study procedures and requirements will be provided. Participants will be included once informed consent has been obtained and documented. Child assent will be documented where appropriate.

### Intervention

The treatment will be IPG objectively measured in millimetres of mercury using the PicoPress® pressure sensor (mediGroup Australia, Melbourne, Australia) [29], and it will be administered post-operatively between days 3 and 5. Participants in the treatment group will be asked to wear the IPG for 23 h/day for a period of 8 weeks. Individual wear time for the IPG will be established through completion of a daily log book for the treatment group. Participants will commence involvement in the study as inpatients on the burn ward and may progress to the outpatient clinic during the study as per normal hospital procedure. Once discharged from the inpatient burn ward, participants will return to the hospital for fortnightly study measurements. Both groups will be reviewed every 2 weeks over the 2-month period to check scar and/or IPG quality (in millimetres of mercury). Surgical intervention, wound care dressings, medication, nutrition, exercise and nursing management of the donor site will be standardized between groups, the sole difference being that one group will have compression therapy for their donor site and the other will not.

The principal investigator will record demographic information, including age, skin type (as assessed using Fitzpatrick skin typing) [30], cause of injury, TBSA burned, depth of injury, surgical procedure undertaken, medication used and time taken to heal (including number of dressing changes and types of dressings used). Smoking status (which may impact on wound healing) will also be recorded. The donor will be considered healed when there is no raw, open or oozing epithelium. A second researcher blinded to the intervention will complete all outcome measures.

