#### Conclusion of assessments

For participants in the IPG group, the principal researcher will measure the amount of pressure in each garment and issue new interim garments if needed, thereby ensuring that pressure remains constant. This concludes the assessment and treatment regime. The participant will undergo the same regime at each subsequent appointment for the period of 8 weeks. At this point, they will be released from the study.

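### Time to healing, one of the aims under Primary objectives, is recorded by the principal investigator and is not clearly assigned to the blinded assessor

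*Protocol article*

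**What the plan says.** Under Primary objectives the protocol article gives an unranked list of five specific aims. One of them is a shorter time to epithelisation.

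The Intervention section assigns the recording of data in one paragraph:

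- It opens with "The principal investigator will record demographic information, including age, skin type". The list that follows ends with "medication used and time taken to heal (including number of dressing changes and types of dressings used".
- It then gives the criterion: "The donor will be considered healed when there is no raw, open or oozing epithelium". No person is named as making that decision.
- It closes with "A second researcher blinded to the intervention will complete all outcome measures".

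Under Conclusion of assessments, for the garment group, "the principal researcher will measure the amount of pressure in each garment and issue new interim garments if needed".

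The Methods/design part of the abstract describes the trial in these words: "This study is a single-centre, single (assessor)-blinded, randomised control trial in patients with burns donor sites to their thighs".

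Measurement tools lists an ultrasound scanner, a colour meter, a garment pressure sensor and a scar scale, and says of them: "These outcome measures will be done every 2 weeks for a period of 2 months". None of these measures time to epithelisation.

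**The concern.** Healing is called by eye against a descriptive criterion, with no instrument. Such an outcome is open to detection bias when the person making the call knows the arm. The Background also reports clinical impressions in favour of the garment, so an unblinded observer's expectation would have a likely direction.

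The article files this outcome with demographic and background items, in the hands of someone whose garment duties reveal the allocation, and then says that every outcome measure is completed blind. If the healing date is in fact set by the principal investigator, a result on one of the primary aims would carry an assessor-blinded label that it has not earned.

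**Working it through.** **1. Who handles time to healing**

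| Question | What the article gives | Where |
|---|---|---|
| Is it a trial outcome? | Yes, one of five aims | Primary objectives |
| Who records it? | The principal investigator | Intervention |
| Who decides that the site is healed? | Not stated; the criterion is a passive sentence | Intervention |
| Who completes outcome measures? | A blinded second researcher, for all of them | Intervention |
| Does a listed tool cover it? | No | Measurement tools and its subsections |
| Who handles garments? | The principal researcher | Conclusion of assessments |

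Two steps are inference. The first is that principal researcher and principal investigator are the same person. This is the natural reading, since the blinded assessor is called the second researcher directly after the principal investigator is named. The second is that this person knows the allocation. The article does not say so, but anyone who measures and replaces garments in one arm only will know it.

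**2. The two ways to read the paragraph**

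- If all outcome measures includes healing, the blinded researcher should make the call, but the only person the text links to a healing time is the principal investigator.
- If it means only the listed tools, healing falls outside the blinding altogether, although it is a primary aim.

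Neither reading gives a clear statement that healing is assessed blind.

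**3. Does it touch the powered comparison?**

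The Sample size section plans "For a minimum clinical difference of 0.5 mm between groups of less than 0.05 and a power of 0.9", with SD 0.5 mm. The usual two-sided formula gives

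n per group = 2 × (1.960 + 1.282)² × 0.5² / 0.5² = 2 × 10.51 = 21.01, rounded up to 22.

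This reproduces the stated 22 per group (the one-sided version gives 18). The calculation rests on thickness, which is measured by ultrasound. Nothing puts that measurement with the principal investigator, so neither the figure nor the comparison changes.

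**4. Illustration of sensitivity**

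From the documents: 22 per group, a 5% level, and re-epithelisation at about 14 days (Background). Assumed: an SD of healing time of 2, 3 or 4 days, normal times rounded to whole days, no true effect, every garment-group date shifted earlier by a fixed amount, and a two-sided Mann-Whitney test. Simulated false-positive rates, approximate:

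| Systematic misdating | SD 2 | SD 3 | SD 4 |
|---|---|---|---|
| none | 5% | 5% | 5% |
| 0.25 day | 6% | 6% | 6% |
| 0.5 day | 13% | 8% | 6% |
| 1 day | 34% | 18% | 12% |
| 2 days | 88% | 55% | 34% |

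A hand check for 1 day and SD 3: the standard error is 3 × √(2/22) = 0.905. The shift in standard errors is 1/0.905 = 1.106. Multiplied by √(3/π) = 0.977 for the rank test, this is 1.080. The rejection rate is Φ(1.080 − 1.960) + Φ(−1.080 − 1.960) ≈ 0.19. That is close to the simulated 18%; the simulation also rounds to whole days.

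**The case against.** The best reply is that to record is not to judge. The neighbouring items on the list (burn area, depth of injury, surgical procedure, medication, dressings) are of the kind copied from the clinical record. The healing criterion names no judge, and the next sentence gives outcome measures to the blinded researcher. The paragraph can be read consistently: the blinded researcher assesses and the principal investigator transcribes. The date could also come from ward care, since the Background uses the same criterion to decide how long the dressings continue. Ward staff would not necessarily be blinded either.

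This stands as far as it goes. A reader might infer that the two statements flatly contradict each other, or that the person delivering the treatment judges healing. The text does not establish either. What the reply does not supply is any sentence that gives the healing decision to the blinded researcher.

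It is also fair that the aims are unranked, so the position of this aim in the list gives it no precedence, and that the one inferential analysis described concerns skin thickness.

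Finally, no part of the document supports any particular amount of misdating. A shift of a quarter of a day is nearly harmless in the illustration.

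**Conclusion.** The concern holds as a failure to assign the assessment clearly, not as proof of an unblinded endpoint. As written, time to healing may be determined by someone who knows the arm and still be reported under an assessor-blinded label. This rests on reading the principal researcher and the principal investigator as one person, and on the absence of any text giving the decision to the blinded researcher.

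Two further conclusions are tempting and are not supported. One is that the trial's powered result is compromised: the ultrasound thickness comparison is not affected. The other is that the false-positive rate is 34% or any other figure in the table: those rates show what a uniform misdating would do under assumed SDs, not what this protocol will produce.

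The point should be fixed, because the outcome is a stated primary aim and the remedy is small.

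**What to change.** - In the Intervention section, take time to healing off the principal investigator's list as an outcome. State that the existing blinded second researcher makes the healed or not-healed call, with the garment already removed as the Standardization section requires before measurement, and that the principal investigator only transcribes the date.
- If healing is determined only at the fortnightly study visits, analyse it as healed or not healed by visit, that is, as interval-censored.
- If an exact date has to come from unblinded ward or investigator records, say so and report time to epithelisation as not assessor-blinded.

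The cost is a change of wording and one data item moved to an assessor who already attends the study visits. The sample size does not change. The real downside is coarser dating: with visits every two weeks and healing expected at about 14 days, much of the information would sit around one or two visits. Photographs at dressing changes could sharpen the dates, but they are an added procedure with their own handling and reading, and oozing is hard to judge from an image. They should be optional and not the core of the change.
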